#### Public participation

In this study, public participation of the participants was used to design an educational social media intervention and evaluate its impact on promoting preventive behaviors.

### Statistical analysis

#### Data management

The obtained data is analyzed in three stages.

Phase 1: Analysis of data from a qualitative study to determine potential domains and items of the researcher-made questionnaire

Phase 2: Factor analysis of the questions to determine the definitive domains and items of the researcher-made questionnaire

Phase 3: Analysis of data obtained from both groups of intervention and control at three time points of before intervention, 1-month and 3-month follow-ups

#### Data monitoring

The data obtained from the qualitative study is analyzed based on Graneheim and Landman algorithms in qualitative content analysis. The MAXQDA software will be used to encode semi-structured interview data.

To evaluate the validity of the structure, factor analysis and scale correlation matrix and the Kaiser_Meyer_Olkin (KMO) Index as well as Bartlett’s test sphericity will be used. The factor structure of the questionnaire is extracted using varimax rotation.

The quantitative data in clinical trial will be analyzed using SPSS V24. Descriptive statistics will include frequencies, means, and standard deviations. The Kolmogorov-Smirnov test will be used to check the normal distribution of data. Moreover, to compare the means between the two intervention and control groups, *T* test is used. Paired *t*-test will be used to compare the means in each group at two points in time, and ANOVA test will be used to compare the means in each group at three points in time. To analyze and evaluate the correlation between demographic variables, correlation tests (Pearson for parametric data and Spearman or Kendall for non-parametric data) and chi-square test will be used.

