## Methods/design

The design of this protocol is a randomized clinical trial. The final purpose is to develop and evaluate a model-based social media intervention regarding behavioral work-related neck pain among school teachers. To reach this aim, the following phases which are shown in Table 1 should be done.

**Table 1 Tab1:** The study overview

Phases and participants	Aim	Methods
Phase 1		
Qualitative study on teachers	Step 1: Identifying occupational factors that cause neck pain, impact of neck pain on daily life activities, neck pain preventive behaviors, and affective factors	In-depth interviews
Researcher	Step 2: Designing of an initial questionnaire	Based on step 1
Phase 2		
Psychometrics evaluation	To validate the questionnaire Preparation of the final questionnaire	By research team factor analysis, varimax questionnaire, rotation, content validity index, and impact score
Phase 3		
Design interventions researcher	Step 1: Intervention group training	Based on social media
Implementation teachers	Step 2: Transfer educational content to intervention group	Based on social media
Intervention evaluation teachers	Step 3: Evaluate the program Identify the impact of the program in the intervention group	Questionnaire checklist

The first phase of the research is a qualitative study that is done through interviewing with 25 teachers. Criteria for entering into this phase of the research are as follows: having a work-related neck pain experience and willingness and ability to share his/her experiences. Data collection will be done through semi-structured interview guild line with the participants. The questions are designed based on the health belief model. Participants are asked questions about their experiences about work-related neck pain, its consequences and effects on their work and life, the extent to which teachers suffer from neck pain, the behavioral factors that cause this problem, and the effective neck pain preventive behaviors as well as the benefits/barriers of doing the behaviors and how they are confident that they could do these behaviors. Based on the content analysis of the collected data from the interview, the main categories based on HBM and items of each domain of the researcher-made questionnaire are determined.

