#### Questionnaire used in this study

The main outcome of the study is promoting of neck pain preventive behaviors that will be assessed using a researcher-made questionnaire. Data collection instrument is a researcher-made questionnaire that is completed and collected in three stages. Therefore, before the intervention, 1 month after the intervention and 3 months after the intervention, the questionnaire is presented to the intervention and control groups for completion. The data obtained in three stages in both groups are analyzed to determine whether the educational intervention is effective in promoting neck pain preventive  behaviors in teachers.

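### The only between-arm test is a t-test of means that, on its plain reading, ignores the baseline score, and the within-arm tests beside it are not marked as descriptive

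*Protocol article*

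**What the plan says.** The protocol article, under Questionnaire used in this study, names the outcome: "The main outcome of the study is promoting of neck pain preventive behaviors". It is collected repeatedly in both arms: "before the intervention, 1 month after the intervention and 3 months after the intervention, the questionnaire is presented to the intervention and control groups". The purpose of the analysis is given in the same section: "The data obtained in three stages in both groups are analyzed to determine whether the educational intervention is effective".

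The tests are listed under Statistical analysis, Data monitoring. There are three for the outcome:

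- between arms: "to compare the means between the two intervention and control groups, *T* test is used";
- within each arm, two times: "Paired *t*-test will be used to compare the means in each group at two points in time";
- within each arm, three times: "ANOVA test will be used to compare the means in each group at three points in time".

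The between-arm test has no stated covariate, no change score and no time point. The section names no ANCOVA, mixed model or group-by-time term. The correlation and chi-square tests that follow are reserved for demographic variables.

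**The concern.** Every listed test that involves time stays inside one arm, and the one test that crosses arms does not mention the baseline. Two things are at stake.

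The first is precision. The baseline behaviour score is likely to predict the follow-up score. A comparison of raw follow-up means leaves that variation in the error term and carries any chance baseline difference into the estimate.

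The second is interpretation. Change within an arm mixes the intervention with drift, retesting and regression to the mean. The outcome is a self-reported questionnaire completed three times, so such changes are plausible in both arms, and only a contrast with control removes them. The plan sets within-arm p-values beside the between-arm one and does not say which decides effectiveness.

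**Working it through.** **Inputs.** From Calculating sample size: 63 per arm before dropout, 95% confidence, 80% power. Not stated there, and therefore assumed: a two-sided test, a standardised difference d, and the correlation r between baseline and follow-up scores. I show r = 0.3, 0.5 and 0.7. Equal variances are also assumed.

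**1. The planned size.** The effect size is not given. With d = 0.5, n = 2(1.960 + 0.842)²/0.5² = 62.8, so 63 per arm. Thus d = 0.5 is consistent with the stated 63, but it is an inference.

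**2. Power with and without baseline.** Adjustment for baseline multiplies the outcome variance by 1 − r², so the effective standardised difference is d/√(1 − r²). Power comes from the noncentral t distribution with noncentrality [d/√(1 − r²)]·√(63/2):

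| Analysis | Effective d | Noncentrality | Power |
|---|---|---|---|
| Follow-up t-test | 0.500 | 2.81 | 79.5% |
| Adjusted, r = 0.3 | 0.524 | 2.94 | 83.1% |
| Adjusted, r = 0.5 | 0.577 | 3.24 | 89.5% |
| Adjusted, r = 0.7 | 0.700 | 3.93 | 97.4% |

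**3. Chance baseline imbalance.** In SD units the baseline difference between arms has standard error √(2/63) = 0.178. The chance that it exceeds 0.2 SD in either direction is 2[1 − Φ(1.12)] = 26%; for 0.3 SD it is 2[1 − Φ(1.68)] = 9%. Given an imbalance b and no intervention effect, the follow-up t statistic is approximately normal with mean r·b/0.178 and SD √(1 − r²). The conditional type I error is then:

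- b = 0.2: 5.5% (r = 0.5) and 5.0% (r = 0.7);
- b = 0.3: 9.9% (r = 0.5) and 13.7% (r = 0.7).

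So a modest imbalance barely moves the error rate, and a larger one, which is less likely, roughly doubles it or more. Averaged over all randomisations the error stays at 5%.

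**4. What within-arm p-values would do if used to judge efficacy.** Suppose there is no intervention effect and both arms drift by the same amount c (in SD units). Each paired test has noncentrality c·√63/√(2(1 − r)) on 62 degrees of freedom. If p is its probability of significance, the pattern of significance in the intervention arm but not in control has probability p(1 − p):

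| Drift c | r = 0.3 | r = 0.5 | r = 0.7 |
|---|---|---|---|
| 0.1 | 9.1% | 10.7% | 14.3% |
| 0.2 | 19.3% | 22.6% | 24.9% |
| 0.3 | 25.0% | 22.8% | 12.3% |

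The product p(1 − p) cannot exceed 25%, so the top of this range is the mathematical maximum. With no drift it is 4.8%, and with a drift of 0.5 SD at r = 0.5 it falls to 2.5%. The documents give neither a drift nor a correlation.

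**The case against.** The strongest reply is that the plan already contains a sound test. The between-arm t-test is the first inferential comparison of the outcome listed, participants are individually randomised (Sampling), and the Discussion says that the programme's effects are judged against control. A follow-up t-test then has the right type I error overall and, on the assumed d = 0.5, essentially the 80% power intended. All of this stands. What remains is lost precision, exposure to chance imbalance and the unlabelled within-arm tests.

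Four stronger readings might be inferred, and the documents do not support them:

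- *Efficacy will be concluded from significance in one arm and not in the other.* No section states that rule. The figures in step 4 show what such a reading would cost if it were made.
- *Baseline is not used at all.* It enters the paired tests and the ANOVA. It is missing only from the between-arm comparison, and even there the text does not say whether raw or change scores are meant; raw means is the plain reading.
- *The ANOVA is a one-way analysis that treats repeated scores as independent.* It stands next to an explicitly paired two-time test, so repeated measures is the more natural reading. It would still stay inside one arm.
- *Table 1 defines the effect as within-arm change.* Its row does say "Identify the impact of the program in the intervention group", but the table is an overview, and the text elsewhere refers to both groups.

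It can also be said that covariates and model terms belong in a statistical analysis plan. That would answer a silent article. This one names its tests, so the matter is what it has fixed and not what it has left out.

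**Conclusion.** The point holds as an improvement that is available almost free; the planned randomised comparison is not invalid. As written, the arms are compared only by a t-test of means, which on its plain reading discards a baseline score that is already collected, and the tests of change are confined to single arms without being called descriptive.

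The gain from adjustment is about 3 to 18 percentage points of power (from about 80% to about 83%, 90% or 97%), depending on a correlation that the documents do not give and on d = 0.5, which is only inferred from the 63 per arm. Should efficacy be read from within-arm p-values, equal drift of 0.1 to 0.3 SD in both arms would produce a false pattern of benefit about 9% to 25% of the time at correlations of 0.3 to 0.7. That second figure is conditional on a use of the tests that the plan does not state but does not exclude.

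**What to change.** In Data monitoring, state that the primary analysis is the between-arm difference in behaviour score adjusted for the baseline behaviour score. Either of these will do:

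- ANCOVA at one named follow-up time; or
- one linear mixed model on the 1- and 3-month scores with baseline score, arm, time and arm-by-time, a random participant effect, and a named time for the primary contrast.

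Report the adjusted difference with its 95% confidence interval. State that the within-arm paired t-tests and the ANOVA, run as repeated measures, are descriptive and that no claim of effectiveness will be drawn from them.

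The cost is wording. No extra participants or data are needed, and SPSS, which the plan already names, can fit either model. One condition applies: each person's questionnaires must be linkable over time. Scoring questionnaire says that they are completed anonymously, so the plan should say that a participant code links them. The paired t-tests already planned need the same link.

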## Discussion

One of the features of this study is paying attention to promoting health in the workplace. This study will investigate the effect of interventions in promoting preventive behaviors and reducing occupational neck pain among teachers. The main framework of this study will be designing a model-based intervention in social media context to prevent teachers’ neck pain.

The strengths of this study include conducting a qualitative study to design a researcher-made questionnaire, psychometric phase of the questionnaire, designing an educational intervention based on HBM, and implementing the specific intervention using social media and finally compare it with the control group to determine its effects. However, if this intervention is cost-effective, its’ flexibility and accessibility makes it easy for users to access educational content easily. One of the weakness points of the study is the self-report procedures of people about their neck pain perception and behaviors. Another limitation of the study is the lack of time for collecting data on 6- and 12-month follow-ups to determine its continued maintained effects which should be considered in future studies.

## Ethics and dissemination

1. Obtaining a license from the Faculty of Medical Sciences of Tarbiat Modares University with ID code (IR.MODARES.REC.1399.163)

2. Registration in Iran Clinical Trial Center with ID code (IRCT20210301050542 N1)

3. Obtaining a letter of introduction from of Tarbiat Modares University for the Ministry of Education in Tehran

4. Obtaining a license from the Education Organization of District 19 of Tehran

5. Obtaining informed consent from the participants in the study by the researcher

6. No need to the write first and last name on the questionnaires

7. Assuring participants that their information is confidential

8. Providing educational content to the control group after the end of the research

### Dissemination policy

The publishing project finding in international journals is welcome. The authors would like to present the program results to teachers’ community and other stakeholders in the Ministry of Education in Iran.

### Ancillary and post-trial care

An ergonomist cooperates with the researchers to do the ancillary and post-trial care in this duty.

### Ethics permission

The Ethics Committee for Health Research of Tarbiat Modares University approved the ethical principles with the following code: IR.MODARES.REC.1399.163. Informed consent form will be obtained from all participants. The data (when ready) will be available from the corresponding author on request.

## Data Availability

The data will be available from the corresponding author on request.
